
### Procedure: Interventions for carers

Interventions will be determined through shared decision-making between the carer and their primary contact CHWS staff member and will be informed by the carer-prioritised needs (CSNAT and other needs), and assessment findings. Depending on the expertise and capacity of CHWS staff, some interventions will be delivered by CHWS staff, while other interventions may require referral to other practitioners or services, within or external to Peninsula Health. Carers will be encouraged to continue other health and wellbeing strategies they may be undertaking at the time of attending the CHWS.

#### Interventions provided by the CHWS or referrals to other practitioners or services.

Following intake assessments at the CHWS, an initial individualised intervention plan will be developed with the carer. This plan will be reviewed regularly to ensure interventions are adapted if necessary to meet changing needs. Interventions will be individualised to the carer and may be changed over time through ongoing shared decision-making between the carer and the CHWS staff, depending on progress and possibly changing needs. The CHWS staff will follow up with the carer to support implementation of one or more intervention options that are within their scope of practice to deliver, through provision of information or resources, through direct intervention provision (e.g., if the Primary Contact is a physiotherapist, and the carer has strength or fitness needs, they may be provided with a tailored home exercise program or participation in a CHWS-based group exercise program), or through other actions as required.

There will be broad flexibility in the type and nature of intervention/s that will be initiated in the first instance, including whether the intervention is delivered by CHWS staff, whether it involves referral to an external service/provider/practitioner, and its mode of delivery (face-to-face, online, or hybrid). If assessments indicate the need for medical review for the carer, they will be informed of this, and with their consent, provided with a letter to their medical practitioner outlining assessment findings, planned interventions, and reasons for recommending a medical review. Information on possible options for interventions are included in Table 2, although this is not an exhaustive list.

**Table 2 pone.0326363.t002:** Examples of intervention options for to be provided to carers by CHWS staff, or through referral to other practitioners of services.

Discipline	Services that may be delivered through CHWS staff	Services that carers may be referred outside of the CHWS for^*^
**Social worker**	Counselling or other therapeutic interventions to explore identified issues; Facilitation of individual or group work sessions focused on relevant topics, such as: strategies to navigate changing relationships, self-care and wellbeing, care planning and accessing supports, advocating for themselves and their care recipient, and the importance of maintaining social connections.	Specialist counselling or therapeutic supports (e.g., to support issues including those relating to family violence, family therapy, mental health, or financial counselling); Group or social activities to support social connection and wellbeing.
**Clinical psychologist**	Brief interventions for anxiety and depression; Psychoeducation regarding the caring role; Interventions to support self-care.	Bereavement counselling; Relationship counselling; Medium to long-term therapy for long-standing concerns, e.g., past trauma.
**Occupational Therapist**	Relaxation, mindfulness and stress management techniques; Energy conservation techniques and associated carer education (e.g., 4Ps: planning, pacing, prioritising, and positioning); Home assessment (where possible) to identify risks and or improve carer health and wellbeing as they perform their carer role (e.g., correct use of equipment in the home); Training for manual handling; Assistive technology to support the carer at home.	Carer respite Specialist sleep intervention
**Physiotherapist**	Exercise options, including provision of (1) a tailored home exercise program; (2) a group exercise program (if CHWS physiotherapist has time capacity and relevant experience to deliver); (3) individual 1:1 physiotherapist supervised exercise program (in limited circumstances, depending on time capacity); or (4) other advice regarding maintaining/improving physical performance; Physical activity advice and support/ motivational interviewing (including opportunities for physical activity with care recipient; or independent of the care recipient); Assistance or advice regarding manual handling including for managing the care recipient, and handling of aids and equipment; • Assessment and advice regarding joint pain; • Assessment and advice regarding the need and use of mobility/gait aids (if required for the carer).	Exercise options not able to be provided through the CHWS, including referral and provision of details of a group exercise program (e.g., tai chi, hydrotherapy) not available through the CHWS physiotherapist, or when unable to attend; • Complex pain management, manual therapy, or pain management options not available through the CHWS (e.g., electrotherapy).
**Other**		**Referrals to external organisations for further assessment or interventions:** Where carers’ needs are not able to be addressed within the CHWS (e.g., outside of scope for the CHWS staff, delay in commencing intervention due to wait-list (if present)), carers will be offered referral to a suitable service or provider external to the CHWS, so that the intervention can be implemented. Examples may include referral to: a geriatrician, a general practitioner or a pharmacist for medical or medication-related issues or review; a dietitian for the management of dietary or nutritional issues; a sleep studies service for further assessment and management of sleep difficulties; or a podiatrist for management of foot pain or other foot problems.

* Data regarding these referrals will be recorded in the carers’ Electronic Medical Records and will be collected as part of the evaluation of the CHWS.

#### Other interventions provided through the CHWS (in addition to those outlined above and in Table 2).

Staff will have a range of publicly available information resources to provide to carers, or for carers to search through a structured online portal. While much of the information resources will be focused on carer health and wellbeing, some are also related to improving the carers’ understanding of the care recipient’s specific health condition/s, possible prognosis, and what to expect and prepare for. Where indicated, carers may be referred to their or their care recipient’s medical practitioner for further details of the care recipient’s status and prognosis.

The CHWS staff will run intermittent education sessions to support carers (may be online, face-to-face, or hybrid), and/or link carers to other existing programs available within the community/other organisations, to address commonly identified issues that may benefit from a group education approach. Opportunities for carer peer support (through face-to-face or online) will be provided.

#### CHWS staff team discussion and communication with medical practitioners and other service providers.

After a carer’s initial appointment or 6 month assessment, and at other times as required, the CHWS team will meet to discuss identified needs, intervention plan, outcome/s and other relevant issues. On these occasions, a letter from the CHWS Primary staff contact will be sent to the carer’s general practitioner (or other service provider, as recommended by the carer) outlining the CHWS staff assessment findings, intervention plan/s, and after the 6 month assessment – outcomes of the intervention and ongoing plans.

#### Subsequent appointments and episode of care.

CHWS staff may schedule face-to-face, phone or online appointments with carers to follow up on aspects of interventions or activities after the first appointment, at a frequency that is mutually agreed upon between the carer and the staff member.

Carer involvement with the CHWS will last an average of 6 months (episode of care), from initial contact to final assessment, **with a standard episode of care being six months duration**, from the time of completion of the initial assessments. The decision regarding discharge timing will be made by the CHWS Primary contact staff member and the carer.

Although it is anticipated that the standard episode of care will be six months, carers with ongoing needs being actively addressed by the CHWS or who have added one or more extra interventions during the 6 month period may opt to continue with the Service beyond the 6 month mark. Those who complete an episode of care with the CHWS can be re-referred if their circumstances change, or new issues arise.

For situations where the person being cared for transitions from home to residential care (for permanent care, not for respite care), or in situations where a care-recipient passes away during the episode of care for the carer, the carer will have the option to continue with CHWS support (with review to determine if needs have changed), or to cease involvement with the CHWS (with re-assessment at this time point if this is acceptable to the carer).

The level of risk for adverse events associated with participating in the CHWS is considered low. If an adverse event occurs, it will be reported to the CHWS Manager, and then to the research team, who will inform the Ethics Committee. The health professional/s involved will provide or organise short term assistance and care as required, including supporting seeking medical support.

### Data collection and statistical analyses

Comprehensive data collection will be established via the Peninsula Health Electronic Medical Records (EMR), including participant profile data, the Carer Support Needs Assessment Tool, core outcomes, and main assessments. Data will be entered by Service staff following each assessment, and will be stored securely on the Peninsula Health site. The UR (unique identifier) for carers who have consented for their data to be accessed to aid evaluation of the CHWS, will be provided to the Peninsula Health ACCESS (intake) team. Members of the ACCESS team will access the relevant assessment and intervention data for participating carers, and will extract de-identified data for carers who consented to participate in the evaluation. Data analysis will be conducted using SPSS. Data will be stored securely on the Peninsula Health password-protected site, and de-identified data for the research team analyses will be stored on the Monash University secure site.

### Sample size calculation

This is a pragmatic evaluation study of a new service at Peninsula Health, which will recruit for a 15 month period, with six month follow-up assessments. In the first 10 months of operation, the CHWS will operate one day/week, and for the subsequent five months, two days/week (to allow time for growth in referral base). Conservatively, we estimate two new referrals/ week on average for the first 5 months of CHWS operations, 4/week for months 6–10, and then for the final five months of recruitment (with the CHWS operating 2 days/week) 8 referrals/week. Based on 48 weeks/year of operation, over the 1.25 years of recruitment for the study, this will mean an anticipated 248 people referred. We estimate that 55% of carers referred to attend the Service will consent to participating in the project (n = 137) and undergo assessment and intervention. A previous intervention study to support carers of older people being discharged home from hospital achieved a significant mean improvement of 0.2 on the total average item score for the primary effectiveness outcome measure in this study – the Preparedness for Caregiving Scale [34] (mean average item score at baseline = 2.67 (0.57 sd) on the 0–4 scale for each item, with a sample of n = 140 (two groups)) [36]. This sample size is also expected to be sufficient for the majority of outcome measures being collected.

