## Abstract

Older carers (≥50 years) of older people (≥65 years) are an important sub-group of carers performing valuable roles in providing informal care but often do not have the time or give priority to supporting their own health and wellbeing. Current services supporting older carers’ health and wellbeing are fragmented and inadequate. Through previous research and co-design activity by our team, an innovative multidisciplinary Carer Health and Wellbeing Service (CHWS) has been developed. The purpose of this protocol paper is to describe the rationale for the CHWS and the methods proposed to evaluate its effectiveness and implementation outcomes. The CHWS commenced in March 2024 at Peninsula Health, Melbourne, Australia. Older carers of older people can be referred from multiple sources, including self-referral. A pre-post mixed methods study design is being utilised. Initial assessments include the Carer Support Assessment Needs Tool (CSNAT) and carer prioritisation of their needs, which guides further assessment and interventions. Assessments will occur at Service intake and 6 months later. The primary effectiveness outcome is the Preparedness for Caregiving Scale, and primary implementation outcomes are reach and adoption. Interviews of carers, referrers and staff, and a cost-utility analysis will be undertaken. The target sample size is 137 carers undertaking assessment and intervention over the 15 months data collection. Generalised linear regression will be used to compare pre- and post-continuous outcome measures. Qualitative data will be thematically analysed. Results will inform future scaling up of this innovative approach to optimising health and wellbeing of older carers of older people.

**Trial registration number:** Australian New Zealand Clinical Trials Registry (ANZCTR) – ACTRN: 12625000245493.

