a)*Reach* will be determined through referrals received, aiming for >80% of appointment slots for all CHWS staff being utilised in the last six months of the study recruitment period; and overall sample size relative to the planned sample size (see analysis and sample size calculation section). Sources of referrals (medical practitioners, allied health professionals, carers themselves) will be reported;b)*Effectiveness* outcomes will mainly include the carer outcome measures (Table 1), and also a *cost-effectiveness* evaluation. A cost-utility analysis will be conducted using a societal perspective over a 12 month time horizon (6 months before the carer’s first appointment and 6 months following the carer’s first appointment). Cost data will include CHWS intervention costs (excluding research costs); carer emergency department presentations and hospital admissions (self-report); the quantity of care provided to the person requiring care, including average weekly hours of care provided by the carer, by other people who are not paid, and by other people who are paid (self-report). In addition, the carer will report the “preferred” and “actual” weekly hours spent on their top three leisure activities (noting when the carer role contributes to the gap between “preferred” and “actual” hours of participation). Effect data will be based on the utility index derived from the EQ-5D-5L [37], measured during the carer’s initial appointment and again at their 6 month follow-up assessment. The change in utility index between initial assessment and 6 months will be used to determine quality-adjusted life years (QALYs) gained or lost by the carer. Cost and effect data will be combined to determine incremental cost-effectiveness ratio (ICER) per QALY gained, with a threshold of <$AUD50,000/QALY gained to determine cost-effectiveness [55].c)*Adoption* will be evaluated through several service system outcomes (percentage completing intervention programs and 6 month assessment, number of interventions undertaken, and number of intervention sessions undertaken with CHWS staff). Acceptability of the service will be evaluated through the CAQ-8 and associated survey items, and interviews of a purposive sampling of carers (after the 6 month assessment), service referrers, and an interview with consenting CHWS staff in the last six months of the intervention, or an exit interview for staff leaving the service;d)*Implementation* includes fidelity of the program as intended (which will be evaluated by members of the research team reviewing 5% of de-identified patients’ assessments and intervention programs implemented against CHWS protocol) and adaptations (CHWS staff will document issues and adaptations made during the CHWS implementation and report these to the research team; and will be asked to comment on adaptations in the staff interviews). Other service-related aspects of implementation will be captured as part of the economic evaluation (e.g., costs, non-attendance at booked sessions);e)*Maintenance* at the individual (carer) level will be evaluated through the proportion of carers completing the 6 month assessment and completing interventions. At the system level, maintenance will be determined through the CHWS being able to continue beyond its initial two year intervention period.

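### The stated referral rates give 280 referrals and 154 carers, which does not reconcile with the stated 248 and n = 137

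*Protocol article*

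**What the plan says.** The section Sample size calculation builds the carer sample from a referral projection.

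- Duration: the study is one "which will recruit for a 15 month period, with six month follow-up assessments".
- Block 1: "we estimate two new referrals/ week on average for the first 5 months of CHWS operations".
- Block 2: "4/week for months 6–10".
- Block 3: "for the final five months of recruitment (with the CHWS operating 2 days/week) 8 referrals/week".
- Calendar and total: "Based on 48 weeks/year of operation, over the 1.25 years of recruitment for the study, this will mean an anticipated 248 people referred".
- Yield: 55% of those referred are expected to consent, giving n = 137.

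The abstract repeats the result: "The target sample size is 137 carers undertaking assessment and intervention over the 15 months data collection". The heading of the procedure subsection on older carers carries the same n.

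Under Implementation (service-related) outcomes, Reach is named as a primary implementation outcome. It has two quantitative elements. One is a target of more than 80% use of staff appointment slots in the last six months of recruitment. The other is "overall sample size relative to the planned sample size", with a pointer back to the sample size section.

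**The concern.** Every input to the projection is printed in one paragraph, and the printed total does not follow from them. The discrepancy then passes through the 55% consent fraction into the planned number of carers.

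Two things depend on that number. First, 137 is the only sample size planned for the pre-post carer evaluation, and the projection is its only stated derivation. The section also quotes an earlier trial's result on the Preparedness for Caregiving Scale (improvement 0.2, SD 0.57, n = 140 in two groups), but calculates no required n from it. Second, the planned number is what achieved recruitment is compared with in one part of Reach. If the plan is understated relative to its own assumptions, the reported percentage of plan is flattering to the service.

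**Working it through.** **Inputs** (all from Sample size calculation): rates of 2, 4 and 8 per week; three blocks of five months; 48 operating weeks per year; 1.25 years; 55% consent.

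**Weeks.** 48 × 1.25 = 60 weeks in total; 48 × 5/12 = 20 weeks per block.

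**Referrals from the stated inputs.** (2 × 20) + (4 × 20) + (8 × 20) = 40 + 80 + 160 = 280. The stated figure is 248. The difference is 32, or 32/248 = 12.9%.

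**Participants.**
- Plan's own step: 0.55 × 248 = 136.4, rounded up to 137. This step reproduces.
- From the stated inputs: 0.55 × 280 = 154. The difference is 17, or 17/137 = 12.4%.

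So the discrepancy lies in the referral total, not in the consent step.

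**Is the 10 + 5 month split firm?** The opening of Methods gives recruitment from 1 March 2024 to 31 May 2025, which is 15 months. The subsection on CHWS staff says staff time doubles in 2025. March to December 2024 is 10 months and January to May 2025 is 5, which matches the sample size section.

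**Other readings that keep the stated weekly rates:**

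| Reading | Referrals |
|---|---|
| 52 weeks/year | 303 |
| 50 weeks/year | 292 |
| 46 weeks/year | 268 |
| 44 weeks/year | 257 |
| 60 weeks in all, with all 5 closure weeks (65 − 60) in the last block | about 263 |
| Blocks of 6/5/4 months | 256 |
| Blocks of 5/6/4 months | 264 |
| Blocks of 6/4/5 months | 272 |

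None gives 248.

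**What would give 248:**
- a last block of 16 weeks: 40 + 80 + (8 × 16) = 248, which makes 56 weeks instead of 60;
- a last-block rate of (248 − 120)/20 = 6.4 per week over 20 weeks;
- a uniform calendar of 248/14 ÷ (5/12) = about 42.5 weeks per year.

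Each changes something the section states.

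**Effect on the Reach comparison, if the stated inputs are right.** Enrolling 137 carers is 137/137 = 100% of the printed plan but 137/154 = 89% of the plan that the inputs imply. Seen the other way, 137 out of 280 referrals would be a 49% yield, not 55%.

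**Power, as an illustration only.** Take a pre-post change of 0.2 and an SD of 0.57 from the section, and assume two-sided alpha 0.05 and a pre-post correlation between 0 and 0.7. The SD of the change is 0.57 × √(2(1 − r)). By the normal approximation, power runs from about 83% to above 99% at n = 137, and from about 87% to above 99% at n = 154, before attrition.

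**The case against.** The strongest reply is that the document shows a disagreement between inputs and total, not which of them is wrong. The authors may have intended 137 and misdescribed a rate, a week count or the length of the last block. In that case 137 stands, the Reach comparator stands, and the 89% disappears. This is correct. A reader might infer from the arithmetic that the planned sample size itself is wrong, but the text does not support that.

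A second reply concerns Reach. A reader might infer that the service could be declared to have met its Reach target with too few carers. The document sets no pass mark for the sample-size ratio. The only numeric Reach target is the one on appointment slots, and it does not depend on 137. What moves is a descriptive percentage, in one of two components.

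A third reply is that little else depends on the figure. Recruitment runs between fixed dates, no stopping rule tied to 137 is stated, and the projection is described as conservative. The point about fixed dates stands: enrolment and analysis would, as far as the text shows, be the same under either number. The word conservative does not explain the gap, because it qualifies the weekly rates, and 248 is presented as what those rates produce.

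Finally, raising the plan to 154 once enrolment is known would be a post hoc change to a benchmark. That is a fair warning about how the correction is made, not a reason to leave the figures unreconciled.

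**Conclusion.** The point holds as an internal inconsistency. The stated inputs give 280 referrals and 154 carers; the document states 248 and 137. The gap is 32 referrals and 17 carers, about 12 to 13% of the stated figures. None of the alternative calendars and block splits checked yields 248 with the weekly rates as written, short of changing a stated input.

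The consequence is conditional and limited. If the stated inputs are right, enrolling 137 would be shown as 100% of plan when it is 89%. If an input was misprinted, 137 remains valid and only the description needs correcting. The document does not settle which case applies. A 16-week last block is one simple explanation, but it is inference.

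The discrepancy should not be read as a threat to power: the printed n is the smaller of the two figures, and under the illustrative assumptions power is above 80% at either. Nor is 137 the only planned number in the document, since staff, referrer and interview samples are given separately. It is the only one for the carer outcome evaluation.

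**What to change.** Before Reach is reported, do one of the following:

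1. Restate the projection as 280 referred and 154 participants; or
2. Correct the input actually used (the last-block rate, the operating weeks or the block length) so that 248 and 137 follow from the text.

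Then use the reconciled number in the abstract, in the heading of the older carers procedure subsection and in Sample size calculation, and name it as the comparator in the Reach definition. Date the correction, and say whether it was made before or after the number enrolled was known, so that a change of benchmark cannot be mistaken for a response to the result.

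The cost is wording only. No further carers, data or analyses are needed. Under the first option, the sample-size percentage within Reach would be lower for the same enrolment.
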